## Abstract

**Background:**

Many Brazilian patients with complex diseases who are treated in tertiary referral clinics have been stable for long periods. The main needs of these patients involve monitoring of risk factors and review of drug prescriptions, which could be satisfactorily done in primary care facilities. The goal of this protocol is to evaluate the safety and effectiveness of telemedicine services to support the transition of patients with stable chronic coronary artery disease from the tertiary to the primary level of care.

**Methods/design:**

We designed a randomized non-inferiority protocol that will include 280 patients with stable coronary artery disease (for at least 12 months). Patients will be selected from the Ischemic Heart Disease Clinic in a tertiary care hospital in southern Brazil. Enrolled participants will be randomized into one of two groups: 12 months of follow-up at the same clinic; or 12 months of follow-up at a primary care facility with clinical support from a telemedicine platform including a toll-free line for physicians (intervention group). In the intervention group, decisions to refer patients to tertiary care during follow-up will be made jointly by primary physicians and medical teleconsultants. The groups will be compared in terms of the primary outcome—maintenance of baseline functional class 1 or 2 after 12 months. Secondary outcomes include control of risk factors and instability of the disease.

**Discussion:**

We intend to determine the effectiveness of using telemedicine to qualify the transition of patients with chronic coronary disease from the tertiary to the primary level of care. This should facilitate the access of patients to the healthcare system, since care will be provided closer to their homes, and provide more opportunities for treatment of severe cases at tertiary care hospitals that are often overcrowded.

**Trial registration:**

ClinicalTrials.gov # NCT02489565 – trial registration date May 13, 2015

## Background

Coronary artery disease (CAD) is characterized by a wide range of clinical presentations. In many patients, CAD remains stable for long periods, with fairly steady symptoms over time, whereas in others the presence of multiple cardiovascular events entails the need for revascularization [1]. With a greater number of diagnoses and increased survival following treatment of acute ischemic CAD, the number of patients experiencing stable angina has increased progressively worldwide. In Brazil, 18 thousand new cases of CAD and 900 thousand new cases of angina pectoris are expected every year [2].

The Brazilian public health care system—the Unified Health System (SUS)—was designed to provide universal, comprehensive healthcare to all Brazilian citizens. However, complex technologies, financial resources, and qualified personnel are currently concentrated in large cities, with marked regional inequality [3]. In Porto Alegre, state capital of Rio Grande do Sul, only about 50 % of CAD patients treated in a specialized outpatient clinic at a tertiary care university hospital (Hospital de Clinicas de Porto Alegre, HCPA) live in the city. The other 50 % are referred from other cities in the state Rio Grande do Sul. Some patients travel as much as 8 h to reach the hospital. This situation also causes overcrowding of the tertiary clinic and restricts access, making it difficult to book urgent appointments and prioritize the most severe cases. The performance of specialized tests and exams is often delayed.

Nevertheless, many of the patients seeking care in Porto Alegre could be managed in their city of origin within the context of primary care, defined as “that aspect of a health services system that assures (…) comprehensiveness of care in the sense that only rare or unusual manifestations of ill health are referred elsewhere, and coordination of care such that all facets of care (wherever received) are integrated” [4]. SUS is based on a logic of referral and counter-referral, according to which less technologically dense services may refer patients for care at greater complexity facilities, namely, hospitals and specialized clinics; and these complex services can refer the patient back for follow-up at primary care facilities that are closer to the patient’s home [5, 6]. Because of structural limitations, including health care professionals who feel unprepared or unsupported to treat situations they deem as complex, the referral and counter-referral system is often bypassed.

In this context, telemedicine provides a useful tool for diagnostic and therapeutic support as well as continuing health education. Telehealth appointments involving workers, health professionals, and managers can be used to clarify doubts about clinical procedures and health actions and answer questions regarding the work process [7].

This article describes a protocol designed to evaluate the use of telemedicine to support the counter-referral of stable CAD patients treated in a tertiary outpatient clinic to primary care facilities, with remote assistance for routine follow-up and decision-making regarding the need for care at the tertiary clinic in the presence of clinical instability. This initiative is intended to facilitate the access to tertiary services for patients with more severe conditions, reduce delays in booking appointments and tests, and ensure delivery of quality care to counter-referred patients.

## Methods/design

### Study design

This randomized non-inferiority trial was designed to compare two groups: CAD patients meeting outpatient clinic discharge criteria, counter-referred from tertiary to primary care for follow-up with telemedicine monitoring (intervention group); and CAD patients meeting outpatient clinic discharge criteria with follow-up at the original tertiary care outpatient clinic (control group).

### Study population and sample size

The study population will be selected among patients from the Ischemic Heart Disease outpatient clinic at HCPA, a tertiary care university hospital in South Brazil. All clinic patients have CAD defined by the presence of at least one of the following: documented history of myocardial infarction, surgical or percutaneous myocardial revascularization, lesion > 50 % in at least one coronary artery assessed by angiography, or presence of angina and positive noninvasive testing of ischemia [8].

Study participants will undergo standard anamnesis and medical examination to verify clinical stability and discharge criteria.

The sample size was calculated as 140 patients in each group—considering a non-inferiority margin of 10 % and incidence of 92 % of the main outcome, that is, maintenance of Canadian Cardiovascular Society Functional Classification (CCS) 12 months after the start of follow-up. This was based on the rate of patients with increase in angina to a higher CCS reported by a previous study for the control group receiving optimal treatment for CAD [9]. An additional 10 % margin was added to account for losses to follow-up. For calculation of sample size, a ß of 0.9 and an α of 0.05 (two-sided) were considered.

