### Randomization

Patients eligible for inclusion will be randomized 1:1 using random block sizes of six and four, by a computerized list provided by randomization.com. The investigator in charge of randomization will not be involved in determination of eligibility or assessment of outcomes. Group assignment will be performed by opening a sealed opaque envelope in front of the patient after signature of the informed consent form and completion of the initial research questionnaire. After that, the groups will be managed as follows (Fig. 1):Telehealth group (intervention group): the patient will be discharged from the tertiary care outpatient clinic and directed to a primary care facility (Basic Health/Family Health Strategy unit) previously identified according to residential address. At the primary care facility, patients will book a routine appointment within two months. For that, the patient will bring the discharge note, comprising all relevant information about the case, medical prescriptions, and a counter-reference note with therapeutic planning. The TelessaúdeRS/UFRGS team will contact the basic health unit and provide access to the telehealth platform for follow-up monitoring. A teleadvisory will be scheduled between the medical teleconsultants and the primary physicians within two months after outpatient clinic discharge to discuss clinical management of the patient. Furthermore, primary physicians can call the support team at TelessaúdeRS/UFRGS whenever they have doubts about the clinical management. Patients will be interviewed by telephone at four and eight months of follow-up using the standardized instrument used at study entry. The calls will be made by independent evaluators, hired and trained specifically for this purpose. An appointment will be booked at 12 months of follow-up for final evaluation of the patient.Control group: patients will undergo the usual flow routine during the study period. Patients will be interviewed by telephone using the standardized instrument at four and eight months of follow-up. An appointment will be booked at 12 months of follow-up for final evaluation of the patient. Ifclinical status is stable, the patient will no longer attend the tertiary outpatient clinic for follow-up.

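### The stated ß of 0.9 is most likely a mislabelled power of 0.90, and relabelling it still does not reconcile the two-sided alpha of 0.05 with 140 patients per group

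*Protocol article*

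**What the plan says.** All the design inputs stand in one paragraph of the protocol article, under Study population and sample size.

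- Size: "The sample size was calculated as 140 patients in each group". The abstract gives the total as 280.
- Margin and outcome rate: "considering a non-inferiority margin of 10 % and incidence of 92 % of the main outcome".
- Losses: "An additional 10 % margin was added to account for losses to follow-up".
- Error rates: "For calculation of sample size, a ß of 0.9 and an α of 0.05 (two-sided) were considered".

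Under Randomization, allocation is 1:1. No other section states a power or a ß. The Statistical analysis section repeats the 10% loss and sets a 0.05 significance threshold, but does not return to power.

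**The concern.** Set beside α in a sample-size statement, ß is the probability of failing to show non-inferiority when it is true, and power is 1 − ß. A ß of 0.9 therefore declares 10% power, which cannot sit beside 140 per group. Since this is the only statement of type II error, a reader has to guess what was meant. The obvious guess, 90% power, does not agree with the two-sided alpha in the same sentence.

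At stake is the one figure that says how likely the trial was to show non-inferiority if the two care pathways are equivalent. It is read when the size is judged before the trial, and again if the result is inconclusive. The number of patients, the margin and the outcome rate are not put in doubt by this point.

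**Working it through.** **Inputs.** From Study population and sample size: outcome rate 0.92, margin 0.10, α 0.05 two-sided, 10% loss, 140 per group. From Randomization: 1:1. Two assumptions are needed. The true rate is 92% in both arms, because the text gives one rate and no true difference. The 10% margin is absolute, in percentage points.

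**Formula.** For a non-inferiority comparison of two proportions with unpooled variance, the evaluable number per group is

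n = (z_α + z_power)² × 2 × 0.92 × 0.08 / 0.10² = (z_α + z_power)² × 14.72,

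where z_α is one-sided. A two-sided 0.05 corresponds to one-sided 0.025 (z = 1.960); one-sided 0.05 has z = 1.645.

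**Step 1: can 140 be reproduced?** Read 0.9 as power (z = 1.282).

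- One-sided 0.05: (1.645 + 1.282)² × 14.72 = 126.06. Dividing by 0.9 gives 140.07. Rounding up to 127 and multiplying by 1.1 gives 139.7, so 140. The stated size is recovered.
- One-sided 0.025, the stated alpha: (1.960 + 1.282)² × 14.72 = 154.67, so 155. Allowing for losses gives 173 (155/0.9) or 171 (155 × 1.1). The stated size is not recovered.

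**Step 2: the literal reading.** With ß = 0.9, power is 0.10 and z_power = −1.282.

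- One-sided 0.05: (1.645 − 1.282)² × 14.72 = 1.9 per group.
- One-sided 0.025: (1.960 − 1.282)² × 14.72 = 6.8 per group.

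With the Farrington-Manning variance the larger figure is about 11. A superiority calculation for 92% against 82% at 10% power gives at most 32 with losses. No variant tried at 10% power comes near 140.

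**Step 3: what power does 140 per group give?** Evaluable after 10% loss: 140 × 0.9 = 126. Power = Φ(0.10/SE − z_α), with SE = √(2 × 0.92 × 0.08 / n).

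- n = 126: SE = 0.0342 and 0.10/SE = 2.926.
- n = 140: SE = 0.0324 and 0.10/SE = 3.084.

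| Evaluable per group | One-sided 0.025 (two-sided 0.05) | One-sided 0.05 |
|---|---|---|
| 126 | 83.3% (ß 0.167) | 90.0% (ß 0.100) |
| 140 (no losses) | 86.9% (ß 0.131) | 92.5% (ß 0.075) |

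**Step 4: sensitivity to the variance.** With the Farrington-Manning restricted variance at one-sided 0.025, power is 77.8% with 126 evaluable and 82.3% with 140. At one-sided 0.05 it is 86.7% and 89.8%. So ß runs from about 0.08 to about 0.22 across these cases.

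**Step 5: is the intended power identifiable from 140?** Not strictly. An equivalence calculation by two one-sided tests, each at 0.05, with 80% power splits ß in half. It therefore uses the same z of 1.282 and also gives 126.06, or 140.07 after dividing by 0.9. A 90% non-inferiority power at one-sided 0.05 is the simplest account of the number in a trial described as non-inferiority, but the number alone does not prove it.

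**The case against.** The strongest reply is that this is a slip of notation. A power of 0.90 at one-sided 0.05 reproduces 140 almost exactly, so the value 0.9 is sound and only its symbol is wrong. The size, margin, outcome rate and loss allowance all stay the same when the symbol is corrected. An inconclusive result would in any case be judged mainly by its confidence interval against the margin, not by the printed ß. This largely stands, and it keeps the point modest.

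It also disposes of a stronger reading that a reader might draw from the literal text: that the trial plans a 90% chance of failing to show non-inferiority when care is truly equal. The documents do not support that. The protocol's own 140 per group rules it out, and nothing shows that a ß of 0.9 entered any calculation. The 2 to 7 patients per group show that the label is wrong; they do not measure harm to the trial.

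What does not stand is that swapping the symbol finishes the matter. Writing 90% power beside the retained two-sided 0.05 would leave a sentence that calls for 171 to 173 per group while stating 140. A reader might equally infer from this that 140 is too small. That does not follow either: at the stated alpha 140 still gives 83% to 87% power under the unpooled formula, and the protocol contains no validly stated power target that this misses.

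**Conclusion.** The point holds as an error in a stated design figure. The printed ß of 0.9 is wrong as written and is most likely a power of 0.90. Once it is read that way, the three figures (90% power, two-sided 0.05, 140 per group with 10% loss) cannot all be true. At the stated alpha, 140 per group delivers about 83% power (ß about 0.17) with 126 evaluable, or 87% with no losses. Power of 90% with 126 evaluable holds only at one-sided 0.05.

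These figures rest on 92% in both arms, an absolute margin of 10 points and the unpooled variance. The Farrington-Manning variance lowers the 83% to about 78%. The finding concerns what the protocol says its power is. It does not show that the design is inadequate or that the sample size must change.

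**What to change.** In Study population and sample size, keep 140 per group and replace the ß figure with the power that this size delivers under the alpha adopted. There are two consistent ways to do so.

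- Keep the stated alpha: power about 83% (ß about 0.17) with 126 evaluable patients per group at two-sided 0.05.
- State power 90% (ß = 0.10), but only if alpha is restated as one-sided 0.05, which corresponds to a 90% two-sided confidence interval, and the primary non-inferiority analysis uses that same level.

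In either case, say that the margin is absolute and that 92% is assumed in both arms, so that the figure can be checked. Relabelling 0.9 as power while leaving the two-sided 0.05 in place should not be done.

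The cost is one or two edited sentences and no extra patients. The first option states a slightly less favourable power. The second accepts a 5% rather than a 2.5% one-sided error rate for declaring non-inferiority, and needs a matching line in the Statistical analysis section.

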### Inclusion and exclusion criteria

Individuals of both genders, aged ≥ 18 years, with a diagnosis of CAD and CCS I or II at the moment of enrollment, without cardiovascular events requiring hospital admission during the previous year, will be selected for the study. Verification of discharge criteria will be performed by the medical team running the clinic, without interference from the investigators.

Patients who have been followed-up at the clinic for less than 1 year, unstable patients needing medication adjustments, patients performing diagnostic evaluation at the moment of enrollment, or those who do not agree with the outcome of randomization will be excluded.

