### Statistical analysis

Continuous variables without normal distribution will be described as mean ± standard deviation or median and inter-quartile range (IQR). Categorical variables will be expressed as percentages. Comparisons between groups will be performed by Student’s *t*-test for continuous variables with normal distribution and Wilcoxon’s test for variables without normal distribution. Fisher’s exact test will be used for categorical variables. Logistic regression analysis will be used to establish the effect of the counter-referral strategy on primary and secondary outcomes at 12 months. Analysis of survival free of events at 12 months will be performed using the Cox multivariate regression and described in Kaplan-Meier survival curves. Variables with *P <* 0.10 in the univariate analyses will be included in the multivariate model. Primary outcome analysis will be according to intention to treat (ITT). Determination of sample size has taken into consideration a 10 % loss to follow-up.

Data will be analyzed in SPSS 18.0 for Windows. Statistical significance is set at *P <* 0.05.

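### As worded, the exclusion of patients who disagree with their allocation acts after randomisation, conflicts with the intention-to-treat analysis and can bias the comparison

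*Protocol article*

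**What the plan says.** The last item in the list of exclusions (Inclusion and exclusion criteria) is that "those who do not agree with the outcome of randomization will be excluded".

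The Randomization section fixes when that outcome becomes known: "Group assignment will be performed by opening a sealed opaque envelope in front of the patient after signature of the informed consent form", and once the initial questionnaire is complete. The arms are open. In the intervention arm, "the patient will be discharged from the tertiary care outpatient clinic and directed to a primary care facility"; controls keep their routine follow-up at the same clinic.

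The Statistical analysis section commits to the full randomised set: "Primary outcome analysis will be according to intention to treat (ITT".

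The design section says "This randomized non-inferiority trial was designed to compare two groups". The sample size was set "considering a non-inferiority margin of 10 % and incidence of 92 % of the main outcome", with a further 10% for losses to follow-up. Refusal after allocation is not mentioned there. Nowhere does the article say that patients who disagree with their allocation are still followed or still analysed in their assigned arm.

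**The concern.** Nobody can disagree with an outcome that does not yet exist. Under the described sequence, the criterion can be applied literally only to a patient who has consented, completed the baseline questionnaire, been randomised and seen the result. It is then an exclusion conditional on the arm.

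Two things are at stake. First, the article promises an intention-to-treat primary analysis and also states a rule that takes randomised patients out of the trial; as written, both cannot be carried out. Second, the arms ask different things of patients. Eligible patients have attended the tertiary clinic for at least a year; one arm discharges them from it and the other changes nothing. If those who decline differ in prognosis from those who accept, removing them leaves a selected intervention arm against a less selected control arm. If they also leave follow-up, no analysis can recover their outcomes.

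**Working it through.** **1. Order of events, from the article**

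- Invitation after a regular clinic appointment, then baseline interview (Interview and questionnaires).
- Signed consent and completed questionnaire, then the envelope is opened in front of the patient (Randomization).
- Disagreement with the result is possible only from this point.
- Primary analysis by intention to treat (Statistical analysis).

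The exclusion therefore falls between randomisation and analysis.

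**2. The plan's own sample size**

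Inputs: 92% in both arms, margin 10 points, power 90% (the article's "a ß of 0.9 and an α of 0.05 (two-sided) were considered", with 0.9 read as power).

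- One-sided α 0.05: n = 2 × 0.92 × 0.08 × (1.645 + 1.282)² / 0.10² = 126.06, so 127 per arm; 127 × 1.10 = 139.7, so 140. This reproduces the stated figure.
- One-sided α 0.025: 154.67, so 155 per arm; 171 or 173 after the 10% allowance. This does not match 140.

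The present point does not depend on which α was meant. What matters here is that the allowance is 140 − 127 = 13 patients per arm and is described as cover for losses to follow-up only.

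**3. Shift caused by the exclusion**

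Let r be the proportion of the intervention arm that refuses, s the success rate of those retained and q the rate refusers would have had. No refusal in the control arm is assumed.

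- Rate in all randomised: (1 − r)s + rq
- Rate after exclusion: s
- Shift = s − [(1 − r)s + rq] = r(s − q)

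With s = 0.92 (the article's figure), and r and q assumed:

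| r | q = 85% | q = 70% |
|---|---|---|
| 5% | 0.05 × 0.07 = 0.35 points | 0.05 × 0.22 = 1.1 points |
| 10% | 0.7 points | 2.2 points |
| 15% | 1.05 points | 0.15 × 0.22 = 3.3 points |

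If q = s, the shift is zero. If refusers would do better, say q = 97% with r = 10%, it is 0.10 × (0.92 − 0.97) = −0.5 points. With refusal in both arms, the shift in the difference is r(s − q) for the intervention arm minus the same quantity for the control arm, so the two partly or wholly offset.

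**4. Effect on the non-inferiority conclusion**

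Put the true difference at the margin: control 92%, all randomised intervention patients 82%. Let g be the shortfall of refusers relative to retained patients. With 10% lost to follow-up there are 140 × 0.9 = 126 controls and 126(1 − r) intervention patients. The observed intervention rate is p = 0.82 + rg. The chance of declaring non-inferiority is Φ[(0.10 + p − 0.92)/SE − 1.96], with SE² = p(1 − p)/[126(1 − r)] + 0.92 × 0.08/126.

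| r | g | p | False non-inferiority at nominal 2.5% |
|---|---|---|---|
| 5% | 5 points | 82.25% | 2.9% |
| 10% | 10 points | 83% | 4.2% |
| 15% | 20 points | 85% | 10.6% |
| 20% | 20 points | 86% | 15.6% |
| 10% | −5 points (refusers better) | 81.5% | 1.9% |

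At one-sided 0.05, the 5%/5-point and 20%/20-point rows become 5.6% and 24.3%. All r and g are assumptions.

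**The case against.** The strongest objection is that the clause sits in a list of enrolment criteria whose neighbours (time at the clinic, instability, ongoing diagnostic work) are all judged before allocation, and the Randomization section says "Patients eligible for inclusion will be randomized 1:1 using random block sizes of six and four". Exclusions then come first, and the clause could be meant for patients who, when invited, would not accept whichever group they drew. The flow diagram, which might show where refusers leave, could not be consulted. This reading is possible and, if intended, leaves no conflict with intention to treat. It does not fit the words, however, and nothing else in the article supplies it. A team applying the text literally would drop patients after opening the envelope.

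A reader might also infer that refusals would fall almost wholly in the intervention arm and that the bias must favour non-inferiority. The documents support neither as a certainty. The Background and Discussion say that about half or more of the clinic's patients come from other cities, some as far as 8 hours away, and the Discussion calls the trips stressful. Some may prefer local care and be disappointed by the control allocation. Nothing says that refusers have a worse prognosis. Everyone enrolled is CCS I or II, meets discharge criteria and has had no cardiovascular admission for a year, which narrows the prognostic range and makes a 22-point shortfall an extreme case.

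Finally, keeping refusers in the analysis has its own drawback. Those allocated to the intervention who go on receiving tertiary care pull the arms together, which in a non-inferiority trial also tends towards declaring non-inferiority. This stands, and it is why screening for willingness before randomisation has to be the main remedy.

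**Conclusion.** The point holds on the article's wording: the criterion is a post-randomisation exclusion tied to the allocated arm, and it conflicts with the stated intention-to-treat primary analysis. It can bias the comparison; it has not been shown that it will, or in which direction. Unequal refusal is likely, because the arms are open and only one loses the tertiary clinic. The 0.35 to 3.3 points, against the 10-point margin, rest on assumed refusal of 5-15% in the intervention arm only and assumed refuser success of 70-85% against 92%. The low end is negligible, and the high end, about a third of the margin, needs both assumptions at their extremes. The text should be corrected regardless, because the defect is cheap to prevent and cannot be repaired later if refusers are not followed.

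**What to change.** 1. Replace the criterion with: *not willing, before randomisation, to accept either group*. Unwilling patients are then lost before allocation, so the comparison is unaffected.
2. State that every patient whose envelope is opened is followed through the existing 4-, 8- and 12-month contacts, unless consent to follow-up is withdrawn, and is analysed for the primary outcome in the allocated arm, including those who decline the allocated care.
3. Report refusals after allocation by arm.
4. Add a per-protocol analysis as a sensitivity check against the dilution caused by retained refusers, noting that it leaves them out again and so is itself open to selection.

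The cost is a wording amendment and the follow-up of a few extra patients through calls and a visit that already exist. The statistical price is some dilution of the contrast, which earlier screening should keep small. If patients have already been excluded under the present wording, their number and arm should be reported.
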